### Inclusion criteria

To be eligible for enrollment in the RCT, participants must meet the following criteria:Aged 15 to 24 years;Speak Nyanja, Bemba, and/or English fluently;Reside in the Matero or Chawama constituency area during the time of recruitment;Meet the following criteria based on selected items from the WHO Multi-Country Study on Women’s Health and Domestic Violence Against Women instrument:◦ GBV Exposure Criterion (Sections 7, 8, and 10): Participant reports any emotional, physical, or sexual violence, including:▪ Emotional or controlling behaviors by a current or most recent intimate partner▪ Physical violence by a current or past intimate partner since age 15▪ Sexual violence by a partner or non-partner since age 15▪ Unwanted or coerced sexual touching or sexual acts before age 15▪ Injury resulting from partner violence at any point in lifeAND/OR◦ GBV Risk/Vulnerability Criterion (Sections 6 and 11): Participant demonstrates elevated vulnerability to GBV, indicated by:▪ Endorsement of violence-supportive or controlling gender norms (e.g., obligation to obey husband, sexual obligation, justification of partner authority)▪ Restricted financial autonomy, including partner control of earnings, financial decision-making, or ability to access money/resources▪ Low confidence in the ability to secure funds independently in an emergencyExhibit moderate depressive symptoms indicated by a score of 10–14 on the 9-item Patient Health Questionnaire (PHQ-9), or common mental disorder (CMD) symptoms (e.g., depression, anxiety) as indicated by a score of 9 or higher on the 14-item Shona Symptom Questionnaire (SSQ-14); andBe living with HIV or demonstrate HIV risk behaviors, as defined by validated items from the World AIDS Foundation survey [58], including unprotected sex, multiple sexual partners, coerced sex, or transactional sex.

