### Power analysis

This RCT is powered only to detect intervention effects on symptoms of CMDs, as measured by the SSQ-14, which is the primary outcome. All other quantitative outcomes—including other mental health measures, HIV engagement indicators, and psychosocial variables—will be treated as exploratory and used to inform effect size estimates and future trial design. With the proposed sample size of 126 participants (63 per arm) and using a two-sided alpha level of 0.05, the study will have 80% power to detect a medium effect size of Cohen’s *d* = 0.5 in SSQ-14 scores, which will be analyzed as a continuous outcome. This is a conservative estimate, selected to reflect a clinically meaningful but smaller effect than that observed in the original Friendship Bench trial, which reported a large effect (*d* ≈ 0.75–0.8) over a 6-month period. Accounting for 30% attrition, the sample size estimate was adjusted to account for an original sample size of 180 participants (90 per group). Since our study primarily measures outcomes at 3 months, a smaller effect size is assumed to avoid overestimating power. Between-group comparisons will be conducted at the 3-month follow-up, prior to the waitlist control group receiving the intervention. At 6 months, only within-group analyses will be conducted to assess sustained changes in the intervention group and pre-post change in the waitlist control group. No between-group comparisons will be performed at 6 months.

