### Quantitative data analysis

We will use descriptive statistics to summarize participant characteristics at baseline, feasibility and acceptability metrics, and other implementation outcomes. To assess baseline differences between participants who complete the intervention and those who drop out, we will conduct bivariate comparisons using independent samples t-tests or Wilcoxon rank-sum tests for continuous variables and chi-square or Fisher’s exact tests for categorical variables.

*Primary outcome analysis (powered):* To assess the effect of the adapted intervention on symptoms of CMDs (SSQ-14), we will use mixed-effects linear regression models. This is the only outcome for which the study is statistically powered, based on detecting a standardized mean difference of Cohen’s d = 0.5 at the 3-month follow-up. The model will include:A random intercept for participants to account for within-subject correlation from repeated measures;A fixed effect for time (baseline vs. follow-up);A fixed effect for study group (immediate intervention vs. delayed control);A group × time interaction term to estimate the differential intervention effect over time.

If the model assumptions (e.g., homoscedasticity, normally distributed residuals) are not met, we will consider using generalized linear mixed models with appropriate link functions and distributional assumptions to reduce the risk of Type I and Type II errors.

*Exploratory analyses:* All other outcomes will be analyzed using mixed-effects linear, logistic, or ordinal regression models, depending on the outcome type. These outcomes include:Mental health outcomes: depression (PHQ-9; binary and continuous), anxiety (GAD-7; continuous), and PTSD (CPSS; continuous) symptoms;HIV prevention outcomes (among HIV-negative or status-unknown participants): consistent condom use, PrEP uptake or readiness, HIV risk behaviors (via WAF), and HIV prevention self-efficacy/readiness (via HPRM);HIV treatment outcomes (among HIV-positive participants): ART adherence, clinic attendance, viral load documentation (if available), and HIV treatment self-efficacy (via HIV-SE);

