*Moderation and mediation analyses (exploratory)*: Post hoc exploratory analyses will assess whether changes in mental health outcomes mediate or moderate the intervention’s effects on HIV-related outcomes. Mental health change scores will be calculated separately for each follow-up period (i.e., 3 months and 6 months post-intervention) by subtracting baseline values from the respective follow-up values. This will allow us to assess both short-term and sustained mental health changes and explore their relationship with HIV-related outcomes over time.Mediation: We will test whether changes in CMD symptoms (SSQ-14), depression (PHQ-9), anxiety (GAD-7), or PTSD (CPSS) symptoms help explain (mediate) observed changes in HIV prevention or treatment outcomes using causal mediation models.Moderation: We will include interaction terms between changes in mental health symptoms and intervention group to assess whether the impact of the intervention on HIV outcomes differs depending on mental health changes. Additionally, we will explore whether baseline levels of early adversity (measured by the Adverse Childhood Experiences International Questionnaire; ACE-IQ) [64], social support (measured by the Oslo social support scale; OSSS-3) [66], and coping self-efficacy (measured by the Coping Self-Efficacy scale; CSE) [65] moderate the relationship between the intervention and mental health or HIV outcomes.

*Adjustment variables and stratified analyses:* HIV status (positive vs. negative/unknown) will be included as a covariate in pooled models to adjust for baseline differences. Stratified analyses by HIV status will be considered if each group has a sufficient sample size to support reliable subgroup modeling (e.g., ≥ 40 participants per group). Given the small overall sample size (*N* = 90, accounting for 30% attrition), such stratified analyses may be underpowered and are therefore considered exploratory and hypothesis-generating only. All models will follow an intention-to-treat (ITT) framework, and statistical significance will be assessed at a two-sided *α* = 0.05, with 95% confidence intervals reported. Non-adherence will be handled by analyzing all participants as randomized (ITT); we will also run a pre-specified per-protocol sensitivity analysis defined as completion of ≥ 4/6 sessions and no major protocol deviations. Missing data will be addressed using mixed-effects models, which provide valid estimates under missing-at-random assumptions.

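### The primary model's random intercept assumes equal SSQ-14 variance at baseline and 3 months; if the 3-month SD is larger, 30% attrition makes the standard error too small

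*Protocol article*

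**What the plan says.** Under Quantitative data analysis, the primary outcome paragraph itemises the SSQ-14 model. Its covariance part is "A random intercept for participants to account for within-subject correlation from repeated measures". The fixed effects are group, the group-by-time interaction and time, given as "A fixed effect for time (baseline vs. follow-up". No separate variance by visit is listed. The next sentence says that generalised linear mixed models will be considered if assumptions such as homoscedasticity or normal residuals fail.

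Later in the same section, missing data rest on this class of model: "Missing data will be addressed using mixed-effects models, which provide valid estimates under missing-at-random assumptions".

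The Power analysis plans for substantial loss: "Accounting for 30% attrition, the sample size estimate was adjusted to account for an original sample size of 180 participants (90 per group").

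The Inclusion criteria admit a woman either on PHQ-9 of 10 to 14 or on "a score of 9 or higher on the 14-item Shona Symptom Questionnaire". The Exclusion criteria remove PHQ-9 above 14 and GAD-7 above 14.

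**The concern.** With a random intercept and independent residuals, every visit has the same variance. The entry rule gives a reason to doubt that here. Some women are selected because their SSQ-14, the primary outcome itself, is at least 9 on a 0-14 scale, whereas the 3-month score has no such restriction. The 3-month SD may therefore exceed the baseline SD.

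If every woman has both visits, this does not affect the test, because the variance of the change is still estimated correctly. If some have only a baseline, it does. The fit then contains more baseline rows than follow-up rows, so the common variance is pulled towards the baseline value and the 3-month mean looks more precise than it is. This affects the only powered test in the trial. Likelihood-based validity under missing at random also depends on a correct covariance model, which the missing-data statement does not say.

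**Working it through.** **The plan's own figure.** For d = 0.5, two-sided alpha 0.05 and 80% power, n per arm = 2 × (1.960 + 0.842)² / 0.5² = 62.8, so 63. Dividing by 0.7 gives 90 per arm, 180 in all. The sample size reproduces and is not in question.

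**Inputs for the check.** From the article: 90 per arm at baseline, 63 per arm at 3 months (27 missing), alpha 0.05. Assumed, because the article gives none: the ratio R of the 3-month SD to the baseline SD, the within-woman correlation r, missingness completely at random, no treatment effect, and two visits in the model. The baseline SD is set to 1.

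**Method.** Under the random-intercept model with common variance s² and correlation ρ, the estimated change in one arm is (3-month mean of completers) − a × (baseline mean of completers) − b × (baseline mean of non-completers). Here a = ρ + 0.7(1 − ρ) and b = 1 − a.

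- The large-sample fit has s² = [63 × (1 + R² − 2ρrR)/(1 − ρ²) + 27] / 153, with ρ minimising 153 ln s² + 63 ln(1 − ρ²).
- True variance: (R² − 2arR + a²)/63 + b²/27.
- Variance the model reports: s² × [(1 − 2aρ + a²)/63 + b²/27].
- With k the square root of reported over true variance, type I error is 2Φ(−1.96k). Both arms contribute equally, so k also applies to the interaction.

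**Worked case, R = 2, r = 0.4.** The fit gives ρ = 0.292, s² = 2.217, a = 0.788 and b = 0.212.

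- True variance: (4 − 1.260 + 0.620)/63 + 0.045/27 = 0.0550.
- Reported variance: 2.217 × [(1 − 0.460 + 0.620)/63 + 0.045/27] = 0.0445.
- k = √(0.0445/0.0550) = 0.90, and 2Φ(−1.763) = 7.8%.

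**Over the range of R (r = 0.4; r hardly matters):**

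| R | k | Type I error |
|---|---|---|
| 0.75 | 1.05 | 4.0% |
| 1.00 | 1.00 | 5.0% |
| 1.05 | 0.99 | 5.2% |
| 1.25 | 0.96 | 5.9% |
| 1.32 | 0.95 | 6.2% |
| 1.50 | 0.94 | 6.7% |
| 2.00 | 0.90 | 7.8% |

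At R = 2 the error is 5.0% with no attrition, 5.8% with 10% missing and 6.7% with 20% missing.

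**Simulation.** REML fits to 12,000 simulated trials per setting agree: 5.9-6.2% at R = 1.25, 6.5-7.0% at R = 1.5 and 7.5-8.3% at R = 2. An unstructured covariance gave 4.6-5.3% with a t reference at every R tried from 1 to 3.

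**Which R is plausible.** Illustrative entry models with assumed score distributions were run both ways. Under the article's either/or rule and its exclusions, 30-62% of women entered with SSQ-14 below 9, R was 1.05-1.32 and the error 5.2-6.2%. If everyone had to score at least 9 on SSQ-14, R was 1.75-2.0 and the error 7.3-7.8%.

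**The case against.** The strongest reply is that the effect may be small or absent. The symptom routes are alternatives, so baseline SSQ-14 is only partly truncated. No SD is published, and equal SDs give exactly 5%. The article does not say whether the screening score doubles as the baseline value; a fresh baseline measurement would soften the truncation. The 30% attrition is called conservative, and with 10% missing the error at R = 1.32 is only 5.3%. All of this stands and limits the size.

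A second reply is that the article already names homoscedasticity and offers a fallback, and that covariance details belong in an analysis plan. This stands only in part. The fallback is merely to be considered, depends on the data, and a change of link or distribution does not by itself let variance differ by visit. The random intercept is a stated choice, not an omitted detail.

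Three stronger readings are tempting but unsupported:

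- That the test simply runs at up to 8%. That end needs nearly every woman to enter on SSQ-14 of 9 or more, which the rule does not require.
- That the treatment estimate is biased under missing at random. The model does carry the wrong slope from baseline to 3 months (0.44 against a true 0.75 at R = 1.5, r = 0.5). If dropout depends on baseline severity similarly in both arms, however, the error is the same in each arm and cancels. Nothing in the article implies opposite patterns by arm.
- That 6-month rows make it worse. The article does not say that they enter the primary model, and it rules out between-group comparison at 6 months.

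**Conclusion.** The point holds in conditional form. The listed model assumes equal baseline and 3-month variance, the entry rule makes a larger 3-month SD plausible, and the planned attrition turns that into a standard error that is too small. Under assumed SD ratios of about 1.05-1.3, type I error is about 5-6% and the standard error is roughly 1-5% too small. At a ratio of 2 the figures are about 8% and 10%. Equal SDs or complete follow-up give 5%, and a smaller 3-month SD gives a conservative test. These figures rest on assumed SDs, two visits, 30% missing completely at random and no treatment effect. This is a modest weakness in the primary test, worth correcting because the correction costs almost nothing.

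**What to change.** In the primary outcome paragraph, replace the random intercept alone with an unstructured within-participant covariance, meaning a separate variance at each visit and freely estimated correlations. Fit it by REML with Kenward-Roger degrees of freedom and keep the fixed effects as they are. Fix this in advance, so that it does not hang on a later check of homoscedasticity. In the missing-data sentence, add that validity under missing at random relies on this covariance being adequately specified.

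The cost is a sentence or two of text. With two visits the model estimates three covariance parameters where it now estimates two. If 6-month rows were included it would estimate six, four more than now. Either is easily supported by 180 women.

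### The stated 80% power is for a comparison of 3-month scores, but the planned primary test is a difference in change, which reaches 80% only if the baseline correlation is about 0.5 or more

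*Protocol article*

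**What the plan says.** The Power analysis section starts from 126 evaluable participants, 63 per arm, and states that "the study will have 80% power to detect a medium effect size of Cohen’s *d* = 0.5 in SSQ-14 scores", "using a two-sided alpha level of 0.05". It then allows for 30% attrition and arrives at 180 enrolled, 90 per group. The Quantitative data analysis section repeats that the primary outcome is powered, "based on detecting a standardized mean difference of Cohen’s d = 0.5 at the 3-month follow-up". The effect size is therefore a difference in scores at one visit.

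The model in that same section has a random intercept per participant, a fixed effect for study group, "A fixed effect for time (baseline vs. follow-up") and "A group × time interaction term to estimate the differential intervention effect over time". No baseline-to-3-month correlation appears in the document.

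On timing, Study outcomes makes 3 months the primary endpoint for comparing the arms, Mental health outcomes places the primary SSQ-14 measurement at 3 months, and Power analysis closes with "No between-group comparisons will be performed at 6 months".

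**The concern.** With one baseline, one follow-up and a free group effect, the interaction estimates (3-month mean minus baseline mean) in one arm minus the same quantity in the other. This contrast carries the sampling error of two baseline means as well as two follow-up means. Randomization makes the true baseline means equal, and the model does not use that fact.

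Whether the contrast is more or less precise than a plain comparison of 3-month scores depends entirely on rho. The power statement has no rho in it, so it describes a different test from the one planned. At stake is the power of the only comparison the trial is sized for. Recruitment is partly on symptom thresholds, which can weaken the correlation between baseline and later scores, so a low rho cannot be ruled out.

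**Working it through.** **Inputs from the protocol.** Two-sided alpha 0.05; d = 0.5 at 3 months; 63 evaluable and 90 enrolled per arm (Power analysis); 1:1 allocation; random intercept, group, two-level time and group × time (Quantitative data analysis). **Assumed:** rho, shown over a range; equal SDs at baseline and 3 months, relaxed in step 5. The 3-month SD is set to 1, so the effect is 0.5.

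**1. The protocol's own figure.** n per arm = 2(1.96 + 0.8416)² / 0.5² = 62.8, so 63. Power at 63 per arm is 80.1% by the normal approximation (79.5% by the noncentral t). Allowing for attrition, 63 / 0.7 = 90 per arm, or 180. All stated figures reproduce, as a two-sample comparison of 3-month scores without rho.

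**2. The planned contrast, complete cases.** Variance of a change score = 1 + 1 − 2·rho = 2(1 − rho). Relative to step 1 the variance ratio is 2(1 − rho), which equals 1 at rho = 0.5 and exceeds 1 below it. At rho = 0.3 the SD of change is √1.4 = 1.183, the effect in those units is 0.5 / 1.183 = 0.423, and power is 66% (65% by the noncentral t).

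**3. The planned contrast with all baselines.** The protocol handles missing data through the mixed model, so the 90 baselines per arm contribute. Variance per arm = (1 − rho²)/63 + (1 − rho)²/90. At rho = 0.3: 0.91/63 + 0.49/90 = 0.01444 + 0.00544 = 0.01989. The standard error of the contrast is √(2 × 0.01989) = 0.199, 0.5 / 0.199 = 2.51, and power is 71%. A 300-run simulation of the random-intercept model with 90 baselines and 63 follow-ups per arm gave 70% at rho 0.3. At rho 0.5 it gave 79%, about two Monte Carlo standard errors below the 83% from the formula.

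**4. The baseline-adjusted 3-month difference.** Variance per arm = (1 − rho²)/63. This is the first term of step 3 without the second, so it is never larger.

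| rho (assumed) | Planned test, 63 complete per arm | Planned test, 90 baselines and 63 follow-ups | Baseline-adjusted, 63 per arm |
|---|---|---|---|
| 0.2 | 60% | 66% | 82% |
| 0.3 | 66% | 71% | 84% |
| 0.4 | 73% | 77% | 87% |
| 0.5 | 80% | 83% | 90% |
| 0.6 | 88% | 90% | 94% |
| 0.7 | 95% | 96% | 98% |

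All entries use the normal approximation; where checked, the noncentral t is up to about one point lower. The second column crosses 80% at rho = 0.5, the third at about 0.46. Evaluable participants per arm for 80% power under step 2 would be 101 at rho 0.2, 88 at 0.3, 76 at 0.4 and 63 at 0.5.

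**5. Unequal SDs.** With k = baseline SD / 3-month SD, the change variance is 1 + k² − 2·rho·k, and the break-even is rho = k/2. If k = 0.6 (assumed), the break-even falls to 0.3, and power at rho 0.2 is about 76% with complete cases. The adjusted variance, 1 − rho², does not depend on k.

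**The case against.** Four objections deserve an answer.

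First, the shortfall is conditional. At rho of 0.6 or 0.7 the planned test has 88% to 96% power, more than stated. This stands: the document does not show that power is below 80%, only that the 80% is not tied to the test planned.

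Second, complete-case figures exaggerate the loss, because every randomized baseline enters the mixed model. This also stands, and it moves the break-even from 0.5 to about 0.46.

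Third, entry thresholds may narrow the baseline SD, which helps a change contrast, while SSQ-14 of 9 or more is only one of two symptom routes into the trial (the other is PHQ-9 10 to 14). The net effect on rho and on the SD ratio is unknown. Hence the range above instead of a single figure.

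Fourth, a group × time interaction on baseline and 3-month data is a standard, unbiased estimator in a randomized trial. That is right, and it limits the point to efficiency and consistency.

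A reader might also infer from the two-level time term that 6-month records would be pooled with 3-month ones, diluting the effect after the waitlist arm has been treated. The documents do not support this. Study outcomes, Mental health outcomes and Power analysis all fix the between-group comparison at 3 months, and the last states "No between-group comparisons will be performed at 6 months". Read with those sections, follow-up means the 3-month visit. Only the wording is loose.

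**Conclusion.** The point holds as a mismatch between the power statement and the primary test, not as proof of an underpowered trial. A reader might conclude outright that the planned analysis lacks 80% power, but that would need a value of rho which the protocol does not give.

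Under equal SDs, the planned test meets the claim from a rho of about 0.46 to 0.5 upward and misses it below; at 0.3 the shortfall is roughly 10 to 15 percentage points. A narrower baseline SD lowers the break-even. Whatever rho is, the planned contrast is never more precise than the baseline-adjusted one, so the present choice gains nothing in precision. It should be corrected, as a free improvement; it does not invalidate the design or the estimate.

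**What to change.** Make the baseline-adjusted difference in 3-month SSQ-14 the single primary test, in one of two forms chosen in advance:

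- a longitudinal model with one common baseline mean for both arms (no group main effect at baseline), with the group × 3-month coefficient as the test; or
- a regression of 3-month SSQ-14 on arm, baseline SSQ-14 and HIV status.

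HIV status is already named as a covariate for pooled models and should stay in either form. The two forms handle participants with a missing visit differently, so the text should name one.

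Add a sentence that follow-up in the primary model means the 3-month visit, as the other sections already imply. If the sponsor prefers to keep the interaction with a free group effect, the power section should state the assumed rho and SD ratio and recompute power for that test.

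The cost is wording only: no new data, no change to 63 evaluable or 90 enrolled per arm, and no loss of power. It should be settled before outcome data by arm are seen, since choosing between the two estimates afterwards would be a post hoc choice on the primary test.

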## Methods

### Study design

We will conduct a two-arm HT1 randomized controlled trial (RCT) to evaluate the effectiveness and implementation of the adapted Friendship Bench intervention, *Mpata Yathu*, on HIV prevention and treatment, and depression outcomes among young women living with or at risk for HIV, with a lifetime history of GBV and depression symptoms in Zambia. This study will have two arms: an intervention group and a waitlist control group. This trial follows a superiority framework, testing whether the intervention improves outcomes compared with the waitlist control group. The SPIRIT figure [51] (Fig. 2; see Additional file 3 for Checklist) illustrates the timeline of enrollment, intervention, assessments, and close-out procedures for the RCT of the *Mpata Yathu* counseling intervention for AGYW exposed to GBV in Zambia. All items from the WHO Trial Registration Data Set are provided in Additional file 1. The intervention is designed to be delivered in six sessions, with one session per week. However, participants will be given up to 3 months to complete all sessions to accommodate common barriers such as caregiving responsibilities, stigma, mobility, and illness [52–55]. Counseling sessions will be scheduled to accommodate participant availability, and lay counselors will track session completion. After screening and enrollment, eligible participants will be randomized in a 1:1 ratio to either group.*Intervention group:* Participants will receive up to six individual counseling sessions between baseline and 3-month follow-up (0–3 months).*Waitlist control group:* Participants will receive usual care from 0 to 3 months, followed by the intervention (up to six counseling sessions) between 3 and 6 months.

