#### Mental health outcomes

The primary outcome is symptoms of common mental disorders (CMDs), assessed using the Shona Symptom Questionnaire (SSQ-14) [59]. The SSQ-14 consists of 14 yes/no items assessing psychological distress, with a score ≥ 9 indicating probable CMD. This outcome will be measured at 3 months and analyzed as a continuous variable, consistent with the original Friendship Bench study, which used SSQ-14 scores as a continuous measure to assess symptom reduction overtime [24]. The SSQ-14 was selected as the primary outcome measure because it is a culturally adapted and validated screening tool developed specifically for Zimbabwean and similar Southern African primary care populations. It captures symptoms of CMDs across emotional, somatic, and functional domains, and demonstrated strong psychometric properties in the original Friendship Bench trial [24].

The secondary outcome is depressive symptoms, measured using the Patient Health Questionnaire-9 (PHQ-9). PHQ-9 scores will also be analyzed using both binary and continuous analysis, consistent with the original Friendship Bench trial [24]. Although eligibility for this study includes a PHQ-9 score between 10 and 14, PHQ-9 will also be analyzed as a binary variable using a cutoff of ≥ 11 to estimate the prevalence of probable depression, as done in the original trial [24]. The PHQ-9 was selected as the secondary outcome due to its global recognition and its use in clinical settings in Zambia. Using the PHQ-9 enables broader comparability with global mental health studies and potential clinical integration. Exploratory mental health outcomes include anxiety and PTSD symptoms, assessed with the Generalized Anxiety Disorder (GAD-7) scale and Child PTSD Symptom Scale (CPSS) [61], respectively. CPPS was validated among children and adolescents in Zambia with good internal reliability (*α*> 0.80) [68].

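### The primary SSQ-14 model can be changed after looking at trial residuals; the change is not needed to protect type I error, can inflate it, and can move the effect off the powered scale

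*Protocol article*

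**What the plan says.** All references are to the Protocol article.

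- **Outcome.** Under Mental health outcomes: "The SSQ-14 consists of 14 yes/no items assessing psychological distress". The score is therefore an integer from 0 to 14. The Power analysis section adds "which will be analyzed as a continuous outcome".
- **Powered effect.** The Power analysis section states "using a two-sided alpha level of 0.05, the study will have 80% power" with 63 evaluable participants per arm. The Quantitative data analysis section describes the powering as "based on detecting a standardized mean difference of Cohen’s d = 0.5 at the 3-month follow-up".
- **Primary model.** The Quantitative data analysis section names a linear mixed model with a participant random intercept, time, group and group by time.
- **Conditional change.** The same section continues: "If the model assumptions (e.g., homoscedasticity, normally distributed residuals) are not met, we will consider using generalized linear mixed models". It asks for suitable links and distributions without naming any, and justifies the change as lowering the risk of both type I and type II error. It names no check or threshold, and does not say which result is primary after a change.
- **Entry.** Under Inclusion criteria, a woman may enter on SSQ-14 of 9 or more, or on PHQ-9 of 10 to 14. Only the first route truncates baseline SSQ-14.

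**The concern.** The model for the one powered test depends on the trial's own residuals and then on judgement. Three things are at stake.

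1. **Type I error.** A model chosen after seeing the data need not keep its 5% level, and the plan presents the change as protecting that level.
2. **Variance.** A binomial or count model with only a participant intercept assumes that, given the participant, scores vary between visits no more than the binomial or Poisson law allows. If distress varies more than that, the standard error of group by time can be too small. A linear model estimates its residual variance freely and does not have this weakness.
3. **Scale.** With a logit or log link the model's effect is an odds or rate ratio, while the sample size was set for a mean difference.

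**Working it through.** **The plan's own figure.** Inputs: d = 0.5, two-sided alpha 0.05, 80% power, 1:1 allocation, 30% attrition.

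- n per arm = 2 × (1.960 + 0.842)² / 0.5² = 2 × 7.849 / 0.25 = 62.8, so 63.
- Power at 63 per arm (normal approximation) = Φ(0.5 × √(63/2) − 1.960) = Φ(0.846) = 80.1%; by t-test, 79.5%.
- Randomised = 126 / 0.70 = 180, or 90 per arm.

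The stated figures reproduce, on the mean-difference scale.

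**Why the linear test is sturdy.** With two visits and complete data, the group-by-time estimate is (mean change, intervention) − (mean change, waitlist), and its test is the two-sample t-test on change scores. Unequal variances at baseline and 3 months do not disturb it, because only the differences enter. With 63 bounded change scores per arm, it does not rely on normal residuals.

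**Simulation under no effect.** 63 per arm, baseline and 3 months, 2,000 trials per scenario; simulation standard error at 5% is √(0.05 × 0.95 / 2000) = 0.5 points. SSQ-14 was drawn as 14 binary items with a normal person effect on the logit scale, with or without extra visit-level variation.

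Assumptions that the article does not supply:
- person SD 0.9 and visit SD 0 in A; 0.7 and 0.7 in B to D; 0.8 and 1.1 in E;
- the share of women entering through SSQ-14 of 9 or more;
- the check: Shapiro-Wilk on conditional residuals, or Levene across visits, at p < 0.05;
- an automatic switch when the check fails, to a model with a participant intercept only (Wald test).

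| Scenario | Baseline mean/SD | 3-month mean/SD | Correlation | Check fails | Linear | Switch to binomial | Switch to Poisson |
|---|---|---|---|---|---|---|---|
| A: no entry filter, no extra visit variation | 8.8/3.0 | 6.4/3.2 | 0.69 | 9% | 4.9% | 5.1% | 4.6% |
| B: no filter, extra variation | 8.7/3.2 | 6.4/3.3 | 0.36 | 44% | 6.0% | 12.9% | 5.7% |
| C: half filtered at 9 or more | 9.6/3.0 | 6.7/3.3 | 0.34 | 75% | 4.3% | 14.3% | 3.6% |
| D: all filtered | 11.1/1.5 | 6.7/3.2 | 0.21 | 100% | 4.0% | 11.0% | 3.8% |
| E: all filtered, more spread | 11.5/1.6 | 6.3/3.8 | 0.15 | 100% | 4.9% | 19.2% | 10.4% |

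The last three columns are type I error. In D the check fails because the entry filter halves the baseline SD relative to follow-up (1.5 against 3.2), yet the linear test is at 4.0%.

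Taking the smallest p-value of the linear, binomial and Poisson models, the worst case of free choice, gave 6.1%, 21.7%, 18.0%, 11.6% and 20.4% in A to E.

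A second null simulation at 63 per arm gave 4.5% to 6.8% for the linear comparison. Switching to the binomial model gave 5.5% without extra visit-to-visit variation and 9% to 13% with it.

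**Scale.** The powered quantity is a difference in mean SSQ-14 points divided by its SD. A logit coefficient is a log odds ratio per item and a log-link coefficient a log rate ratio. The 80% power statement does not carry over to either.

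**The case against.** The best defence is that the sentence commits to little. It says only that another model will be considered, and that it should be suitable; an overdispersed model would meet that description. The random intercept is listed for the linear model, so the fallback's random structure is open. The article is condensed, and the check, link and distribution could be set in an analysis plan that is not shown. A generalised model can keep an identity link, or be used to report a model-based mean difference.

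Much of this stands, and it rules out two stronger readings that a reader might infer.

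- **That the switch is nearly certain.** The PHQ-9 route admits women with SSQ-14 below 9, the mix of routes is not given and no check is named. The simulated range of 9% to 100% reflects that.
- **That the switch would raise type I error.** This depends on the model chosen. A Poisson switch was below 5% in three of five scenarios, and a binomial switch was at 5.1% without extra visit-level variation. The inflated figures describe an assumed check, an automatic switch and a particular fallback, not a rule that the article writes down.

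What does not stand is that this is only detail left for later. The article itself states that the primary model is conditional on the residuals, and gives error control as the reason. Filling in the fallback would not remove the dependence on the data, and the reason is not borne out.

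**Conclusion.** The point holds in a conditional form. The article allows trial residuals plus discretion to change the primary SSQ-14 model. The linear test needs little protection: its type I error was 4.0% to 6.8% across the simulations. A switch can make matters worse: about 9% to 19% for a binomial model with a participant intercept alone when scores vary between visits beyond that intercept, about 5% when they do not, and about 4% to 10% for a Poisson model. Less visit-level variation than assumed would move the binomial figure back towards 5%. With a logit or log link, the result would also leave the scale on which d = 0.5 was powered.

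The sizes rest on assumed SSQ-14 variances, correlations and entry mix, on complete data at two visits, and on the assumed check. The case for fixing the primary model does not depend on their exact values. The sample size is unaffected. This should be changed before outcome data are examined.

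**What to change.** Delete the conditional sentence and put in its place:

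- The linear mixed model is the primary analysis of SSQ-14 whatever the residuals show.
- The result is the between-group difference in mean SSQ-14 points at 3 months, from the group-by-time term, with a 95% confidence interval and robust (sandwich) or bootstrap standard errors.
- Any generalised linear mixed model is a sensitivity analysis, named in advance with its link and distribution, and allowing overdispersion (for example beta-binomial variance or an observation-level random effect). It does not replace the primary result.

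This costs wording only: no added participants or data, and 63 evaluable and 90 randomised per arm still apply. The downside is a possible small loss of efficiency if scores pile up near the floor or ceiling of the scale; the sensitivity analysis would help to show whether that matters.
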